## Abstract

**Background:**

Hyperuricemia (HUA) is a metabolic disorder characterized by elevated serum uric acid levels resulting from dysfunction in purine metabolism and/or inadequate uric acid excretion. It is an independent risk factor for many chronic diseases and is associated with a poor long-term prognosis. Existing uric acid-lowering drugs often lead to numerous adverse reactions, resulting in poor patient compliance and limited clinical application. Therefore, this study aims to investigate the effect of Kuiyuan Chewing Tablet (KYCT) on serum uric acid (SUA) levels in patients with HUA, and to seek a safe alternative therapy for reducing uric acid.

**Methods and analysis:**

This study is a multicenter, randomized, double-blind, parallel-controlled trial. HUA patients who meet the inclusion criteria will be randomly assigned in a 1:1 ratio to either (1) the control group (placebo of KYCT, specifications: 0.3g per tablet, 1.2g per dose, twice a day, taken with warm water 30 minutes after meals) or (2) the experimental group (KYCT, specifications: 0.3g per tablet, 1.2g per dose, twice a day, taken with warm water 30 minutes after meals). Both groups will receive dietary control, comorbidity prevention, and health education during the intervention period. The primary outcome will be the proportion of subjects with SUA levels <420 umol/L. Secondary outcomes will include the proportion of subjects with SUA levels <360 umol/L, the percentage change in SUA levels from baseline to each visit, the maximum percentage change in SUA levels from baseline to the third month, the number of gout attacks, changes in body measurements (weight, waist circumference, hip circumference, BMI), blood pressure, blood lipids, fasting blood glucose levels, and the proportion of subjects reporting gout attacks (cumulative up to each visit). Each group of patients will be assessed at baseline, as well as at the 4th, 8th, and 12th weeks.

**Discussion:**

This study aims to evaluate the effects of a 12-week treatment with KYCT on patients with HUA. We hypothesize that compared to placebo, KYCT would significantly improve SUA levels without provoking significant adverse reactions. These findings potentially pave the way for a safe and effective alternative therapy for HUA.

## Background

Hyperuricemia (HUA) is a metabolic disorder resulting from disturbances in purine metabolism and/or impaired uric acid excretion. It is clinically diagnosed when the serum uric acid level exceeds 420 µmol/L (360 µmol/L for females) on two separate occasions (1). Relevant data suggest that the incidence of HUA and gout has been increasing year by year, with a trend toward younger age groups, due to changes in lifestyle and dietary patterns. HUA is now the second most common metabolic disorder after diabetes (2). Reports indicate that the prevalence of HUA varies among ethnic groups, ranging from 2.6% to 36% (3–5). Large-scale epidemiological investigations in mainland China have revealed that the prevalence of HUA in the general population is 17.4%, ranging from 15.5% to 24.6% in different regions and exhibiting an increasing trend (6). However, the reported prevalence is significantly higher in some countries. For instance, the prevalence of HUA is 21.2% for men and 21.6% for women in the United States (7) while it is 25.8% (34.5% for men and 11.6% for women) in Japan (8).

HUA is a global illness that can lead to gout, with some severe cases resulting in tophi, joint deformities, and complications such as kidney and cardiovascular disease. Numerous studies suggest that HUA is an independent risk factor for chronic kidney disease, hypertension, cardiovascular disease, and diabetes, and that it is linked to poor long-term outcomes (9–13). Elevated blood uric acid levels are the primary cause of HUA and associated complications, underscoring the vital necessity for effective uric acid level control. Pharmacological treatment is recommended for asymptomatic HUA patients in Asian countries such as Japan and China (14). According to Chinese guidelines (2), urate-lowering therapy should be initiated in asymptomatic HUA patients with serum uric acid levels of ≥ 540 μmol/L or ≥ 480 μmol/L with comorbid conditions like hypertension, dyslipidemia, and diabetes.

According to Chinese guidelines, Allopurinol, Febuxostat, and Benzbromarone are the first-line drugs for lowering uric acid levels (2). Allopurinol is particularly suitable for patients with increased uric acid production, but it might cause fatal allergic reactions in Asian populations (15, 16). Allopurinol is metabolized by the kidneys and must be started at a low dose when renal function is normal, limiting its clinical application (17). Studies have shown that Febuxostat, another uric acid-lowering drug, may increase the risk of cardiovascular disease and may also induce gout attacks (18). Benzbromarone is especially useful for patients with HUA and gout who have decreased uric acid excretion, but caution should be exercised in patients with renal insufficiency and kidney stones. Moreover, it should be supplemented with a large amount of water intake to increase excretion and alkalize the urine. Caucasians have reportedly experienced acute liver failure as a result (19). Low compliance among patients taking uric acid-lowering medications is a result of the safety issues with these medications and the underdiagnosis of the disease among patients. The results of a 2018 meta-analysis showed that the average compliance of uric acid-lowering drugs was 47% (ranging from 17% to 83.5%) (20).

Therefore, it is crucial to develop new medication for HUA that can lower blood uric acid levels efficiently with minimal side effects. Exploring natural therapeutic agents from medicinal plants that have high efficacy and low toxicity is a promising alternative treatment option. In recent years, edible Sunflower (Helianthus annuus L.), a member of the Asteraceae family and a native of North America, has been widely cultivated in China, Russia, Argentina, France, and other countries (21). Kuiyuan Chewing Tablet(KYCT) is extracted from the heads of the sunflower plant, which mainly contains flavonoids, coumarins, and phenolic acids. It helps lower uric acid levels, reduces inflammation and pain, repairs the liver and kidneys, and is widely used as a dietary health product in China. Preclinical studies indicate that KYCT’s primary active component, sunflower head extract (SHE), exerts dual-pathway hypouricemic effects. First, SHE suppresses uric acid synthesis by inhibiting xanthine oxidase (XO) activity via its polyphenolic constituents, as evidenced by 32-41% XO activity reduction in hyperuricemic models (22). Second, SHE enhances uric acid excretion through coordinated regulation of urate transporters: downregulating reabsorption transporters (URAT1/GLUT9) and upregulating secretory transporter ABCG2, thereby shifting renal/intestinal transport toward net excretion (23). These synergistic mechanisms may explain KYCT’s preclinical efficacy comparable to allopurinol and benzbromarone, though clinical validation remains warranted.

In this study, we aim to investigate the effect of Sunflower Bud Chewing Tablet on serum uric acid (SUA) in patients with HUA and to seek safe alternative therapy for uric acid reduction. We will conduct a randomized parallel-controlled trial to determine the impact of KYCT on patients with HUA. We hypothesize that KYCT would significantly improve SUA levels without provoking significant adverse reactions compared to placebo. In addition, these findings potentially pave the way for a safe and effective alternative therapy for HUA.

## Materials and methods

### Study objective

This multicenter, randomized, double-blind, placebo-controlled trial aims to investigate the efficacy and safety of KYCT for reducing serum uric acid (SUA) levels in patients with HUA. We will conduct a 12-week, multicenter, double-blind, randomized controlled trial to ascertain its effectiveness in treating HUA. We hypothesize that KYCT will significantly outperform a placebo to lower SUA levels in patients with HUA over 12 weeks of treatment.

### Study design

This randomized, double-blind, multicenter, parallel-controlled trial started and ended recruitment in July 2023. The 1-year study will randomize participants into experimental and control groups. Assessments will be conducted at baseline, weeks 4, 8, and 12. The study flowchart is shown in **Figure 1**. This study has been approved by the Ethics Review Committee of Guang’anmen Hospital, China Academy of Chinese Medical Sciences (approval No.2023-057-YW). Written informed consent will be obtained from all patients prior to enrollment. This study will follow the Consolidated Standards of Reporting Trials (CONSORT) guidelines (24).

**Figure 1 f1:**
[figure not shown]
Trial flow chart.

### Study setting

This study will recruit 126 eligible participants from multiple medical institutions, including Guang’anmen Hospital of China Academy of Chinese Medical Sciences, Huashan Hospital affiliated to Fudan University, Shenzhen Traditional Chinese Medicine Hospital, Inner Mongolia Autonomous Region Hospital of Traditional Chinese Medicine, and Liaoning University of Traditional Chinese Medicine Affiliated Hospital.

### Inclusion criteria

(1) Age 18–70 years (at the time of obtaining informed consent), any gender; (2) Meet the diagnostic criteria for asymptomatic HUA; (3) Blood uric acid level > 8.0 mg/dL (480 μmol/L) at enrollment after 1 month or longer of low purine dietary control; (4) No history of acute gout attack before enrollment; (5) Normal electrocardiogram at enrollment; (6) Able to swallow Tablet; (7) Voluntarily participate, able to comply with regular follow-up and complete patient logs, and sign an informed consent form.

### Exclusion criteria

(1) Secondary HUA caused by renal disease, hematological disorders, medication, tumor radiotherapy/chemotherapy, organ transplantation, or other reasons; (2) Use of allopurinol, febuxostat, benzbromarone, probenecid, or Chinese herbal medicine with uric acid-lowering effect within 4 weeks prior to enrollment; (3) History of stroke, transient ischemic attack, myocardial infarction, heart failure (NYHA class II-IV), or coronary artery surgery (such as angioplasty, stenting, or bypass surgery); (4) Abnormal liver function tests with aspartate aminotransferase (AST), alanine aminotransferase (ALT), or γ-glutamyltransferase (GGT) levels higher than 1.5 times the upper limit of normal at screening (Visit 1); (5) Abnormal renal function tests with serum creatinine (SCr) levels higher than 1.5 times the upper limit of normal at screening (Visit 1); (6) Co-existing malignant tumors or psychiatric disorders; (7) Known allergy or intolerance to any component of Kuiyuan chewing tablet or the investigational medicinal product excipients; (8) Known hypersensitivity or history of severe asthma exacerbated by nonsteroidal anti-inflammatory drugs (NSAIDs) or aspirin, or any component of NSAIDs or aspirin; (9) Use of oral corticosteroids for 10 or more consecutive days or use of intramuscular, subcutaneous, or intra-articular corticosteroids within 1 month prior to screening (Visit 1); (10) Co-existing autoimmune diseases; (11) Use or need for anticoagulants (such as aspirin, other salicylates, heparin, or warfarin) or antiplatelet agents (such as clopidogrel or ticlopidine); (12) Use or need for diuretics; (13) History of alcohol or drug abuse or daily use of analgesics for any reason; (14) Pregnancy, lactation, or planned pregnancy within 3 months after the last dose of investigational medicinal product; (15) Participation in other clinical studies within 3 months prior to screening (Visit 1); (16) Other conditions deemed unsuitable for this clinical study by the investigator.

### Withdrawal criteria

#### Decision made by the investigator

1) Occurrence of allergic reactions or serious adverse events that require discontinuation of the trial according to the investigator’s judgment; 2) Occurrence of other complications or physiological changes during the trial that make it inappropriate for the participant to continue; 3) Poor compliance by the participant; 4) other situations deemed inappropriate for the participant to continue by the investigator or in which continuing the trial is difficult according to the investigator’s judgment.

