### Handling of dropout cases

Subjects who withdraw prematurely from the trial or are lost to follow-up will be contacted to complete a final assessment. Every effort will be made to collect efficacy and safety data for these subjects. Reasons for premature withdrawal will be documented in the case report form and trial conclusion form.

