### Random allocation and blinding

A double-blind, single-mimic approach was chosen because the placebo Tablet in the control group had the same appearance, specifications, size, and odor as the Kuiyuan chewable Tablet. All test drugs were provided by Beijing Qino Biotechnology Co., Ltd. and had uniform internal and external packaging.

A two-level blind design was adopted, with the first level corresponding to the group (such as Group A and Group B) for each case number and the second level corresponding to the treatment (test group and control group) for each group. The Institute of Basic Clinical Medicine of Traditional Chinese Medicine, China Academy of Chinese Medical Sciences, established the random coding table. The two-level blind bottoms were separately sealed, with two copies each, and stored at the Guang’anmen Hospital of the China Academy of Chinese Medical Sciences and Beijing Qino Biotechnology Co., Ltd., respectively.

Each coded investigational drug has a corresponding emergency letter, which contains a piece of paper indicating the type of drug that code is to be used in case of emergency unblinding. The emergency letter should be sealed and sent along with the investigational drug of the corresponding code to each clinical research center, where it should be kept by the center and not opened unless necessary. If a severe adverse event occurs or a subject needs to be rescued and it is necessary to know the treatment the subject received, the investigator may unblind the subject. Once unblinded, the subject will be withdrawn from the trial and treated as a dropout, and the reason for withdrawal should be recorded in the case report form by the investigator. All emergency letters will be collected along with the case report form at the end of the trial for the unblinding audit.

A two-step unblinding method was used. The data were locked after all case report forms were entered into the database, and the data underwent questioning, verification, and blinding audits. The investigator who kept the blind code then performed the first unblinding, revealing groups A and B. A biostatistician entered The data into the computer and linked it to the data file for statistical analysis. After the statistical analysis was completed, a second unblinding was performed to identify the treatment groups and the experimental and control groups.

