#### Efficacy endpoints

##### Primary efficacy endpoint

The proportion of participants who maintained SUA levels <420 umol/L at week 12 (SUA levels were uniformly determined by uricase-peroxidase coupling assay, as described in Appendix 1).

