### Data analysis

The complete analysis set (FAS) and per protocol set (PPS) were used for efficacy evaluation analysis. The safety set (SS) was used for safety indicator analysis; since concomitant medications may affect efficacy and safety, the overall combination therapy was analyzed using the SS. General data was analyzed using the FAS and PPS. The last observation was carried forward for efficacy analysis for participants who withdrew prematurely. Dropouts with baseline data were included in efficacy analyses using the last observation carried forward. Excluded cases were not included in the efficacy statistical analysis, but those who received at least one treatment and had at least one safety record participated in the adverse reaction analysis.

To address potential confounding from lifestyle modifications, we will implement a three-pronged strategy to differentiate the specific effects of KYCT from those attributable to dietary control and health education. First, the double-blind placebo-controlled design ensures both groups receive identical lifestyle interventions, with KYCT administration being the sole therapeutic distinction between arms. Second, our primary analysis will employ analysis of covariance (ANCOVA) adjusting for key lifestyle covariates including physical activity levels (measured in MET-minutes/week) and daily purine intake (quantified through 24-hour dietary recalls). Third, sensitivity analyses will examine treatment effects in predefined adherent subgroups (≥80% protocol compliance for both medication intake and lifestyle recommendations) to assess outcome robustness against potential lifestyle adherence variations.

Furthermore, to address potential heterogeneity in treatment effects across subpopulations, three methodological safeguards have been incorporated: First, stratified randomization by baseline sUA tertiles (7.0-7.5, 7.6-8.5, >8.5 mg/dL) and sex ensures balanced subgroup distributions. Second, pre-specified Bayesian hierarchical models with regularizing priors [N(0,1)] will estimate subgroup effects while pooling information across multicenter clusters. Third, all subgroup comparisons will apply Benjamini-Hochberg FDR correction (<10%) within stratification categories, with results explicitly interpreted as exploratory hypotheses per CONSORT extension guidelines.

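### Poor compliance and emergency unblinding lead to withdrawal from the trial, and nothing secures a week-12 SUA for these participants or ranks an observed one above the carried-forward value

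*Protocol article*

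**What the plan says.** The primary endpoint is fixed in time: "The proportion of participants who maintained SUA levels <420 umol/L at week 12" (Primary efficacy endpoint).

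Two rules take participants out of the trial, not only off study drug:

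- Withdrawal criteria, Decision made by the investigator, lists "Poor compliance by the participant" as a ground for withdrawal. It is at the investigator's discretion.
- Random allocation and blinding makes removal automatic after an emergency code break: "Once unblinded, the subject will be withdrawn from the trial and treated as a dropout".

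Handling of dropout cases then provides some follow-up: "Subjects who withdraw prematurely from the trial or are lost to follow-up will be contacted to complete a final assessment". It adds: "Every effort will be made to collect efficacy and safety data for these subjects". No time point is attached to either sentence.

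Data analysis fills the gap by carrying values forward: "The last observation was carried forward for efficacy analysis for participants who withdrew prematurely", and "Dropouts with baseline data were included in efficacy analyses using the last observation carried forward".

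**The concern.** Poor compliance and emergency unblinding are not random events. The first reflects adherence and possibly tolerability. The second follows a severe adverse event or a need for rescue. Both may be related to treatment and to the SUA that would have been seen at week 12.

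For these participants the plan ends trial participation and then permits an earlier value to serve as the week-12 result. A week-4 or week-8 value taken on KYCT may show control that is gone by week 12. A carried baseline value is always a failure, whatever the participant's later course. Which effect dominates depends on when and why each arm loses people, so the direction cannot be known in advance.

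A better imputation method chosen later would not recover a week-12 measurement that nobody took. That makes this a matter of protocol wording as well as of analysis.

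**Working it through.** **1. The passages side by side.**

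| Question | What the article states |
|---|---|
| Does the event end participation in the trial? | Unblinding: always. Poor compliance: if the investigator so decides. |
| Is any later contact planned? | Yes, a final assessment and efforts to obtain efficacy and safety data. |
| Is that contact placed at week 12? | Not stated. |
| Is a week-12 SUA after withdrawal forbidden? | No. |
| Does an observed week-12 SUA replace the carried value? | Not stated; the carry-forward rule is given without exception. |

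**2. A carried baseline is always a failure.** Inclusion criteria require SUA above 480 µmol/L at enrolment; response requires SUA below 420. The randomisation strata in Data analysis start lower, at 7.0 mg/dL, which does not fit that entry limit. At the article's own conversion (480/8.0 = 60 µmol/L per mg/dL), 7.0 × 60 = 420, which is still not below the threshold.

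**3. The plan's own dropout figure.** Sample size calculation gives 53 per group and 15% dropout: 53/(1 − 0.15) = 62.4, rounded up to 63 per group and 126 in total. This step reproduces. The 53 itself does not: at 60% vs 30%, two-sided 0.05 and power 0.8, the pooled formula gives 42 and the continuity-corrected one 49. The stated figure is on the conservative side and does not bear on this point. Fifteen percent of 63 is 9.45 participants per arm. This is total dropout, including self-withdrawal and loss to follow-up.

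**4. Size of the possible bias.** Let *d* be the fraction affected in each arm, *c* the response rate after carrying forward, and *t* the true week-12 rate (1 = KYCT, 0 = placebo). The unaffected respond at the planned 60% and 30%.

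Analysed difference = [(1 − d)·0.60 + d·c₁] − [(1 − d)·0.30 + d·c₀]

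True difference = the same with t₁ and t₀ in place of c₁ and c₀

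Bias = d·[(c₁ − t₁) − (c₀ − t₀)]

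*Case A, on-drug value carried.* Assumed: c₁ = 0.60, t₁ = 0.30, c₀ = t₀ = 0.30. Bias = 0.30·d.

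*Case B, baseline carried in both arms.* Assumed: c₁ = c₀ = 0, t₁ = 0.45, t₀ = 0.30. Bias = −0.15·d.

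| d | Participants per arm (of 63) | Case A: analysed vs true | Bias A | Case B: analysed vs true | Bias B |
|---|---|---|---|---|---|
| 3% | 1.9 | 30.0 vs 29.1 | +0.9 points | 29.1 vs 29.55 | −0.45 points |
| 5% | 3.2 | 30.0 vs 28.5 | +1.5 points | 28.5 vs 29.25 | −0.75 points |
| 15% | 9.5 | 30.0 vs 25.5 | +4.5 points | 25.5 vs 27.75 | −2.25 points |

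The values of *d*, the true rates and the carried rates are assumptions. The article supplies only 60%, 30%, 15% and 63. The 15% row is a ceiling within the planned dropout allowance, because it assigns all dropout to these two routes.

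**The case against.** The strongest reply is that Handling of dropout cases already asks for what is wanted: contact, a final assessment and every effort to obtain efficacy and safety data. A reader might infer from the withdrawal rules that week-12 SUA is lost by rule and that safety follow-up is cut short. The article does not support that. It forbids no later measurement and explicitly seeks further data. What remains is that the effort is not tied to week 12, and that the carry-forward rule does not yield to a week-12 value if one is obtained.

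A reader might also infer that the plan always equates stopping drug with leaving the trial. That is too general. Under Intervention group, study medication stops at SUA below 180 µmol/L with no statement that the participant leaves. The planned sensitivity analysis in participants with at least 80% compliance implies that less adherent participants stay in the data. The point is limited to the two named routes, and for poor compliance to those whom the investigator chooses to withdraw.

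A third reply is that an article leaves detail to the full protocol. This holds for the missing compliance threshold, which is not pressed here. The timing of the final assessment may also be given there. But the withdrawal rules and the carry-forward rule are stated in the article itself, and as stated they leave the week-12 outcome open to replacement.

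Finally, the arithmetic measures the error of carrying forward, so it should not be added to any separate criticism of that method. This is correct. The withdrawal rules matter because they create occasions for that error.

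**Conclusion.** The point holds in a limited form. For poor compliance at the investigator's discretion, and for emergency unblinding always, the article ends trial participation, does not fix the final assessment at week 12, and applies last observation carried forward without giving precedence to an observed week-12 SUA. Outcome-related substitution of the primary endpoint is therefore possible, in either direction.

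No single figure follows. If on-drug values are carried at 60% against a true 30%, the overstatement is about 0.9 points at 3% affected and 1.5 points at 5%. It reaches 4.5 points only if all 15% dropout came from these two routes, and a reader should not take that as the expected size. If baseline values are carried and the true rates are 45% and 30%, the bias is −0.45 to −2.25 points over the same range. Against a planned difference of 30 points these are modest amounts, and the number affected is unknown and may be small. The case for change rests on a documented mechanism and a cheap remedy, not on a large demonstrated bias.

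**What to change.** **Protocol text.** In Withdrawal criteria, Handling of dropout cases, and Random allocation and blinding, leave whether and when drug is stopped as it is. State that these participants remain in follow-up for their scheduled visits, including week-12 SUA and safety tests, unless they withdraw consent or cannot be contacted.

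**Data analysis.** State that they are analysed in their randomised arm, that an observed week-12 SUA is used in place of a carried-forward value, and that imputation applies only when no week-12 value can be obtained.

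**If follow-up is already complete.** Study design says that recruitment started and ended in July 2023, so missed visits may be beyond recovery. In that case apply the precedence rule to whatever week-12 values were collected, and report the timing and reason of withdrawal by arm.

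**Cost.** For someone withdrawn at the week-4 visit or later, at most two visits already on the schedule; three for someone unblinded before week 4. The estimate will include time off drug and may be slightly less favourable to KYCT.
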